#### **(5) Enhancing cardiorespiratory fitness can improve immune function and enhance the health status of elderly individuals**

Given the critical value of cardiorespiratory fitness in maintaining health, contemporary clinical practice is gradually focusing on the cardiorespiratory fitness of elderly individuals. Studies have shown a significant correlation between immune levels and cardiorespiratory function, with immune factor levels positively correlating with cardiorespiratory fitness. Improving cardiorespiratory fitness not only aids in enhancing a patient's immune function but also benefits the recovery of cardiovascular and metabolic diseases, and osteoporosis, among others. Therefore, it is essential to intensify attention and research on cardiorespiratory fitness in elderly individuals, particularly in identifying suitable techniques and methods to improve and enhance cardiorespiratory fitness, elucidating their role and value in anti-immune aging, enhancing immune function, and chronic disease rehabilitation.

#### **(6) Moxibustion Enhancing Cardiorespiratory Fitness Needs Quantification and Optimization**

The role of moxibustion in reducing fatigue and improving fitness has substantial evidence in normal individuals, athletes, and lower limb arterial disease patients. The preliminary confirmation of moxibustion improving cardiorespiratory fitness exists. However, there is inconsistency in clinical protocols for improving cardiorespiratory fitness through moxibustion, mainly in terms of acupoint selection and technical parameters for moxibustion. Currently, the commonly used acupoints for moxibustion to combat fatigue and increase fitness are primarily Shenque, Guanyuan, and Zusanli. As for moxibustion parameters, they vary widely, with moxibustion sessions ranging from 1 to 3 times per week and session durations ranging from 0.5 to 1 hour. Hence, in

the clinical protocol for moxibustion to improve cardiorespiratory fitness, it is necessary to study and define suitable technical parameters based on precise assessments to achieve quantification and optimization of the clinical protocol.

Given the progress of domestic and international research, it is believed that there is a widespread decline in cardiorespiratory fitness among the elderly, which is potentially associated with various chronic diseases and immune aging. Moxibustion, with its ability to warm meridians, and regulate Qi and Blood, may enhance cardiorespiratory fitness and immune function in elderly individuals. Conducting empirical research on moxibustion clinical protocols based on an objective analysis of cardiorespiratory fitness can further quantify and optimize these protocols. This endeavor aims to provide technical specifications for the promotion and application of moxibustion in tonifying Qi and Blood, improving cardiorespiratory fitness in the elderly, and enhancing immunity.

-----

## **2. Research Objectives**

The primary goal is to apply and promote the clinical protocol of moxibustion for tonifying Qi and Blood, thereby enhancing cardiorespiratory fitness in elderly individuals. The aim is to effectively assist the elderly in maintaining health, improving their quality of life, and contributing to elderly care initiatives. This study intends to observe the variations in primary outcome indicators ( $VO_{2peak}$ , AT value, serum central carbon metabolites, 6MWD, etc.) and adverse events occurring under the intervention of moxibustion. It aims to evaluate its effectiveness and safety.

-----

## **3. Experimental Design Type, Principles, and Procedure**

(1) Experimental Design Type: Randomized Controlled Trial

(2) Principles of Experimental Design:

Sample Size Calculation:

The sample size was determined based on our prior pilot investigation. A mean difference in  $VO_{2peak}$  of  $2.6 \text{ ml} \cdot \text{kg}^{-1} \cdot \text{min}^{-1}$ , with a standard deviation (SD) of 3.0 was observed between the moxibustion and control groups. The estimation conducted via the website (<https://sample-size.net/sample-size-means/>). Approximately 29 participants each group are needed to detect a clinically significant difference in outcome measures at a 5% significance level and 90% statistical power. Considering an estimated dropout rate of 15%, the final sample size required will be 35 for each group, resulting in 105 participants. To recruit this number of participants, we anticipate a study period of 9 months based on our pilot study.

Randomization: Stratified Random Allocation

Control: The study includes apparently healthy elderly individuals, with no underlying diseases. Based on recognized principles of effectiveness, safety, and comparability,

sham moxibustion and no intervention are chosen as controls.

-----

#### **4. Participant Selection**

This study will recruit participants from the neighboring community of the Second Affiliated Hospital of Nanjing University of Traditional Chinese Medicine through brochures, posters, and community outreach programs.

##### **(1) Inclusion Criteria:**

- Men or women aged between 60 and 80;
- No cognitive impairment;
- Decreased CRF ( $VO_{2peak} < 20\text{ml}\cdot\text{kg}^{-1}\cdot\text{min}^{-1}$  or  $6\text{MWD} \leq 450$  meters).

##### **(2) Exclusion Criteria:**

- Acute stage of serious diseases, such as acute myocardial infarction, acute myocarditis, unstable angina;
- With any other absolute contraindications to CPET or the Six-minute walk test (6MWT);
- With any underlying diseases, such as hypertension, diabetes, coronary heart disease;
- Currently using other Chinese and Western medicines that affect the results of this study;
- Other physical injuries that affect the evaluation of observation indicators, such as lower extremity pain, nerve and muscle diseases;
- Respiratory symptoms within one month;
- Other conditions that may reduce the possibility of enrollment or complicate enrollment, such as frequent changes in the living environment, are likely to cause a loss of follow-up.

##### **(3) Dropouts:**

- Participants experiencing severe adverse events, as judged by the physician, necessitating termination of their clinical trial participation.
- Occurrence of significant deviations during the implementation of the clinical trial protocol, such as poor compliance, difficulties in evaluating moxibustion efficacy, etc.
- Significant lifestyle changes including but not limited to alterations in diet, and exercise habits.
- Weight fluctuation of more than 5kg.
- Participants express unwillingness to continue the clinical trial during the trial process and request to withdraw from the study under the overseeing physician.
- Unforeseen circumstances hindering the participant's involvement, such as severe accidents, sudden serious illnesses, or death.

(4) Handling of Dropouts:

Dropout Criteria: Participants who, after providing informed consent and being screened as eligible for randomization, fail to complete the specified treatment or observation period according to this protocol will be considered dropout cases.

Handling of Dropouts:

- Researchers should attempt to contact participants who drop out through home visits, scheduled follow-ups, phone calls, letters, etc., to inquire about the reasons for withdrawal, record the last intervention time, and complete as many assessment items as possible.
- In case of dropout due to allergies, adverse reactions, or ineffective treatment, appropriate treatment measures should be taken based on the participant's actual condition.
- All information related to dropout cases should be properly preserved for archival purposes and for statistical analysis in the comprehensive dataset. No additional recruitment of dropout patients is necessary.

(5) Exclusion of Cases:

- Cases that do not meet the inclusion criteria but fulfill exclusion criteria.
- Cases that have not used the experimental intervention.
- Cases without any data after randomization.
- Before statistical data analysis, the decision to exclude cases will be made after discussion among statisticians and principal investigators.

-----

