## 11. Statistical Analysis

### (1) Statistical Analysis Plan and Statistical Software

- Full Analysis Set: Refers to the ideal set of participants as close as possible to the intention-to-treat principle (mainly analyzing all randomized participants). This dataset is derived by excluding participants from all randomized participants in the least and reasonable manner. For missing values of the primary variables, carry-forward estimation will be used, bringing forward the results closest to a single observation of the missing data in the trial, and ensuring consistency between the number of participants evaluated for efficacy at the endpoint and those at the start of the trial.
- Statistical Analysis Contents: Actual number of enrolled participants in three groups, dropout and exclusion cases, demographic and other baseline characteristics, compliance, efficacy analysis, and safety analysis.

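### Subjective post-randomisation events are listed as reasons for dropout, so deviating from the intervention is not kept apart from leaving the study, and obtainable outcome data may be lost differently by arm

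*Protocol*

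**What the plan says.** Protocol Section 4 (3) lists reasons for dropout. Three of them concern conduct or change during the trial:

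- significant deviations in carrying out the plan, with these examples: "such as poor compliance, difficulties in evaluating moxibustion efficacy, etc";
- a lifestyle rule with no threshold: "Significant lifestyle changes including but not limited to alterations in diet, and exercise habits";
- a body-weight rule, the only one with a limit: "Weight fluctuation of more than 5kg".

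Section 4 (4) applies dropout status to people who have consented and been found eligible for randomisation: those who "fail to complete the specified treatment or observation period according to this protocol will be considered dropout cases". Staff are to try to reach them, "record the last intervention time, and complete as many assessment items as possible". Their information "should be properly preserved for archival purposes and for statistical analysis in the comprehensive dataset".

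Section 4 (5) is a separate list of cases to be excluded. It includes "Cases that have not used the experimental intervention" and leaves the exclusion decision to discussion between statisticians and principal investigators before the analysis.

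Section 11 (1) defines a full analysis set close to intention to treat ("mainly analyzing all randomized participants"), with carry-forward for missing primary values. The Abstract also names an analysis of data collected in line with the protocol. Section 6 (5) defines compliance as moxibustion sessions received over sessions planned. Section 5 gives the blank control group no treatment.

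**The concern.** Poor compliance, a hard-to-judge response and a change in habits all arise after allocation. A sound plan records them and goes on measuring the participant. Here they share a list with severe adverse events and withdrawal of consent, so the list reads as reasons for ending participation.

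Three features make this a matter of bias as well as of lost numbers.

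- The criteria are largely subjective. Apart from the 5 kg limit there is no threshold, two of the three bullets are open-ended, and no blinded judge is named. Difficulty in evaluating efficacy could be invoked after a result has been seen.
- The session ratio exists only for the two arms that attend for 60 sessions.
- Once follow-up lapses, the missing value is replaced by an earlier one.

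At stake is the comparability of the arms that randomisation provides. A later analysis plan cannot recover measurements that were never taken.

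**Working it through.** **1. The plan's own sample size.** Section 3 gives a VO2peak difference of 2.6 with SD 3.0, 5% significance, 90% power and 15% dropout; Section 11 (2) makes the test two-sided.

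- Normal approximation: n = 2 × (1.960 + 1.282)² × (3.0/2.6)² = 2 × 10.51 × 1.331 = 27.98, so 28 per arm.
- Two-sample t-test: 28.97, so 29 per arm, as stated.
- Dropout: 29 / (1 − 0.15) = 34.1, so 35 per arm; 3 × 35 = 105, as stated.

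The figure reproduces. Power for 2.6 is 90.0% with 29 per arm and 94.7% with 35, if the effect is not diluted by non-compliance.

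**2. The passages side by side.**

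| Question | Section 4 (3) and (4) | Section 4 (5) | Section 11 (1) |
|---|---|---|---|
| Do compliance, lifestyle or weight end participation? | Yes, as dropout reasons | Not named | Not addressed |
| Are these cases kept for analysis? | Yes | Not on the list, but exclusion by discussion is open-ended | Yes, in the full set |
| Is the later outcome measured? | Best effort | – | If missing, carried forward |

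The loss therefore lies in measurement, and it enters the full analysis set through carry-forward. In the analysis of protocol-conforming data these cases would probably be left out altogether.

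**3. Illustration of size.** Apart from 35 per arm, SD 3.0 and the 15% dropout allowance, every input is assumed. Outcome is change from baseline. Leaving occurs in one arm only, and those with worse outcomes are more likely to leave. ρ is the assumed correlation between leaving and outcome. There are 20,000 simulated trials per setting. Fifteen per cent of 35 rounds to 5 people, that is 5/35 = 14.3%. Carry-forward is modelled as baseline carried forward.

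True effect 0, bias in ml/kg/min (type I error):

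| | ρ = 0 | ρ = 0.3 | ρ = 0.5 |
|---|---|---|---|
| All followed and analysed | 0.00 (5.1%) | +0.01 (5.1%) | 0.00 (5.4%) |
| Leavers kept, baseline carried forward | 0.00 (5.2%) | +0.20 (6.1%) | +0.34 (8.4%) |
| Leavers left out | +0.01 (5.0%) | +0.23 (6.2%) | +0.38 (8.5%) |

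Departures of about 0.01 from zero in the first row and the ρ = 0 column are simulation noise.

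True effect 2.6, baseline carried forward: the estimate is 2.23, 2.43 and 2.56 for ρ = 0, 0.3 and 0.5. The first follows by hand: 2.6 × 30/35 = 2.23.

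With 5% leaving (2 of 35), ρ = 0.5 and no true effect, the bias is +0.16 with carry-forward and +0.17 with leavers left out.

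**4. Reading.** Carry-forward removes little of the bias from outcome-related leaving, and it shrinks a true effect even when leaving is unrelated to outcome. If those who leave are the ones doing better, the sign under no true effect reverses. If a week 4 or week 8 value is carried instead of baseline, the sizes will differ.

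**The case against.** The strongest reply is that nobody is deleted. Section 4 (4) keeps dropouts for analysis and requires active efforts to reach and assess them, Section 11 (1) keeps them in the full set, and the exclusion list in Section 4 (5) names none of these events. This stands. A reader might infer that the main analysis would set compliant, stable moxibustion participants against unselected blank controls. The documents do not support that for the full analysis set, and the lifestyle and weight rules cover the blank arm too.

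A reader might also infer that every contrast is biased. That is too strong. Moxibustion and sham share the same frequency, duration and number of sessions, so loss through poor compliance need not differ between them. Bias from leaving participants out is zero if leaving is unrelated to outcome. Nor is the deviation bullet wholly confined to the treated arms: blank controls can breach the instruction to avoid other interventions or miss measurement times. Only the session ratio cannot apply to them. That extra exercise might follow from feeling fitter is plausible, but the protocol does not say so.

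What the reply does not answer is that follow-up after dropout is best effort. Section 9 (4) also pays compensation to those who complete all planned treatments and assessments, which gives a dropped participant less reason to return. Gaps are then filled by a method that does not correct for selective leaving. Set definitions may be detailed in an analysis plan that is not shown, but whether the visits take place is decided here.

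**Conclusion.** The concern holds as a risk. The protocol makes largely subjective post-randomisation events reasons for dropout and does not separate deviating from the intervention from leaving the study. Obtainable outcome data may be lost in a way that depends on arm and outcome.

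The exposure is clearest in contrasts with the blank arm and in the analysis of protocol-conforming data. Neither size nor direction can be fixed from the documents. The simulated figures, from 0.00 to +0.34 ml/kg/min under carry-forward with no true effect and 2.23 in place of 2.6 when leaving is unrelated to outcome, rest on assumed one-arm leaving, assumed correlations and baseline carry-forward. They show what is possible and are not an estimate for this trial. The matter should be corrected, though it does not invalidate the design.

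**What to change.** In Section 4 (3), take the deviation/compliance, lifestyle and weight bullets off the dropout list and record these events as protocol deviations. State that such participants are still invited to the week 4, 8, 12 and 24 assessments already scheduled in Section 6 (6) and are analysed in the arm to which they were randomised. Use the deviations only to define the per-protocol sensitivity set.

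Reconcile Section 4 (3) to (5) with the full analysis set in Section 11 (1), so that one text says who stops participating, who is still measured and who is analysed. In particular, "Cases that have not used the experimental intervention" needs rewording, since read literally it describes the whole blank arm.

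Leave the bullets on severe adverse events, withdrawal by the participant and unforeseen circumstances unchanged.

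The cost is protocol wording, because the visits already exist. The small downside is that the estimate will reflect actual adherence and may be slightly smaller.

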**Blank Control Group:**

The blank control group will receive no treatment and will be instructed not to undergo any interventions that might affect cardiorespiratory fitness until the trial is completed. Measurements for the blank control group will follow the designated time points as the Moxibustion and Sham Moxibustion Groups.

-----

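### The rule excluding cases that did not use the experimental intervention does not fit the blank control arm, names no analysis set, and as workably read can remove non-starters from moxibustion and sham only

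*Protocol*

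**What the plan says.** Four parts of the protocol bear on a randomised participant who never starts the allocated intervention.

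- **Section 4, item (5), Exclusion of Cases.** One listed ground is "Cases that have not used the experimental intervention". The next is "Cases without any data after randomization". The item closes by saying that, before the analysis, "the decision to exclude cases will be made after discussion among statisticians and principal investigators". It names no arm and no analysis set, and does not say that the discussion is blind to allocation.
- **Section 4, item (4), Handling of Dropouts.** Participants found eligible for randomisation who "fail to complete the specified treatment or observation period according to this protocol will be considered dropout cases". Their information is to be preserved "for statistical analysis in the comprehensive dataset".
- **Section 5(2), Blank Control Group.** "The blank control group will receive no treatment and will be instructed not to undergo any interventions" that might affect fitness until the trial ends. This arm is measured at the same time points as the other two.
- **Section 11(1), Full Analysis Set.** The set is meant to approach intention to treat, "mainly analyzing all randomized participants", and is reached by as few exclusions as is reasonable. Missing primary values are carried forward, "ensuring consistency between the number of participants evaluated for efficacy at the endpoint and those at the start of the trial".

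The Abstract adds that the primary efficacy measures are analysed on the full analysis set and on data collected according to the protocol. Nothing says which of the two the item (5) exclusions serve.

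**The concern.** A no-treatment arm has no intervention to use, so the rule has no sensible meaning there. An analyst who tries to apply it must read it as meaning people allocated to an intervention who never began. That event can occur in two of the three arms only.

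Dropping non-starters is safe when not starting cannot depend on the allocated arm. Here it can. Moxibustion and sham ask for 60 sessions over 12 weeks; blank control asks for none. A person who would decline that burden is deleted if allocated to moxibustion or sham and kept if allocated to blank control. If such people differ in fitness from those who accept, the arms being compared are no longer the arms that were randomised, and the difference is created by the exclusion rule itself.

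The protocol also gives two instructions for the same person. Under item (4) a randomised non-starter has not completed the specified treatment, so is a dropout whose data are kept for analysis. Under item (5) that person is excluded.

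**Working it through.** **1. The plan's own figures.** Inputs from section 3: difference 2.6 ml/kg/min, SD 3.0, 5% significance, 90% power, 15% dropout. Section 11(2) makes the test two-sided.

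- Normal approximation: n = 2 × (1.960 + 1.282)² × (3.0/2.6)² = 27.98, so 28 per group.
- Exact t-based power is 88.96% at 28 per group and 90.03% at 29, so the t-based answer is 29, as stated.
- Dropout: 29/0.85 = 34.1, so 35 per group, and 3 × 35 = 105.

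These figures reproduce, and the exclusion rule does not enter them.

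**2. What the wording covers.**

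| Reading | Moxibustion | Sham | Blank control |
|---|---|---|---|
| Literal; sham device counts as experimental | non-starters | non-starters | all 35 |
| Literal; only real moxibustion counts | non-starters | all 35 | all 35 |
| Workable: allocated an intervention, never started | non-starters | non-starters | nobody |

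If every allocated person started, the two literal readings would leave 105 − 35 = 70 and 105 − 70 = 35 participants. Those counts show only that the wording cannot be used as it stands. The rest of the check uses the third row.

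**3. Bias on the workable reading.** Let a fraction f of each randomised arm be people who would not start an intervention if allocated one, and let their VO2peak without treatment average b below the rest. Suppose moxibustion has no effect and the mean of the others is m.

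- Blank control keeps everyone: mean = m − f × b.
- Moxibustion after deletion: mean = m.
- Spurious difference = f × b, in favour of moxibustion.

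The protocol gives neither f nor b. Assumed range: 2 to 5 of 35 non-starters, and b from 1 to 3 ml/kg/min.

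| Non-starters of 35 | b = 1 | b = 2 | b = 3 |
|---|---|---|---|
| 2 | 0.06 | 0.11 | 0.17 |
| 4 | 0.11 | 0.23 | 0.34 |
| 5 | 0.14 | 0.29 | 0.43 |

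The ends of the range are (2/35) × 1 = 0.057 and (5/35) × 3 = 0.429. Against the planned difference, 0.057/2.6 = 2% and 0.429/2.6 = 16%. If non-starters were fitter than the rest, the sign would reverse.

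If non-starters stay in both arms, each mean is m − f × b and the spurious difference is zero.

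**4. The sham contrast.** The rule can act in both moxibustion and sham, and the two schedules match. Equal f and b in both arms give a difference of f × b − f × b = 0. The rule builds no imbalance into this comparison.

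**5. Power under the rule.** Exact t-based power for a true difference of 2.6 with SD 3.0 is 94.7% at 35 versus 35, 94.1% at 33 versus 35 and 92.9% at 30 versus 35. The loss of numbers is minor; the issue is bias.

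**The case against.** **A reader might infer that the rule deletes the blank control arm.** The documents do not support that. The Abstract plans 35 blank controls, section 5(2) requires their measurement, section 11(1) plans reporting for three groups, and item (5) sends exclusions to a discussion first. The literal reading shows faulty drafting and is not a forecast.

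**A reader might also infer that the rule and the full analysis set cannot both hold.** That is too strong. Section 11(1) says mainly, not always, all randomised participants, and it allows minimal reasonable exclusions. The equal-numbers phrase belongs to the carry-forward sentence and can be read as applying within the set. What stands is tension: section 11(1) itemises no permitted exclusions, item (5) is the only list in the protocol, and a rule that can act in two of three arms is hard to call minimal and reasonable. The conflict between items (4) and (5) remains even on the generous reading.

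**The rule may be meant for the protocol-adherent data.** It may, and the analysis plan, not shown, could say so. But the protocol does state a rule, without that limit. Confining it to that set is what the fix does.

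**The decision is made by discussion before analysis.** This makes exclusion less than automatic. Section 10(4) refers to records of a blind review, but item (5) does not require blindness to arm, and nobody can apply this rule without knowing who is a blank control.

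**The bias is assumed and may be smaller.** This stands. The inputs come from no part of the protocol, and neither does their direction. Even 5 of 35 (14%) is close to the whole 15% dropout allowance, which covers every reason for leaving. Some non-starters would have no later data and would go under the next bullet anyway, which lowers the marginal effect of this one.

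**Conclusion.** The concern holds as a defect of drafting and analysis-set definition, with a real route to bias. The rule does not fit a no-treatment arm, is tied to no analysis set, and contradicts the dropout handling stated just above it. Applied in the only workable way, it gives an arm-dependent exclusion after randomisation that affects moxibustion versus blank control and sham versus blank control, and leaves moxibustion versus sham without a built-in imbalance.

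The size, about 0.06 to 0.43 ml/kg/min, is an illustration. It rests on the assumed number of non-starters, on their being less fit, and on blank control holding a similar share of such people. The planned 29, 35 and 105 are unaffected. Severity: should be fixed before the data are analysed.

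**What to change.** Amend section 4, item (5), and section 11(1) as follows.

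1. Remove non-use of the experimental intervention as a ground for exclusion from the full analysis set.
2. State that randomised participants who never start stay in that set, in their allocated arm, in line with the dropout handling in item (4).
3. Use not starting the intervention only to define the per-protocol (protocol-adherent) set, with a definition for each arm. For blank control it could rest on keeping to the instruction to avoid other interventions.

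The separate bullet on cases without data after randomisation need not change.

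The cost is a short amendment and some dilution of the estimate. If starters gain 2.6 and non-starters gain nothing, 2 to 5 non-starters of 35 give expected differences of 2.6 × 33/35 = 2.45 to 2.6 × 30/35 = 2.23 ml/kg/min. With all 35 per arm measured and SD 3.0, the t-based power formula used above gives 92.1% to 86.5%, against 94.7% with no non-starters. The upper end is a pessimistic count. This dilution pulls the estimate towards no effect and reflects the effect of being allocated to moxibustion, whereas the exclusion can produce a difference where none exists.
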